### Measuring individual psychological stress levels

The effect of the interventions on individual psychological stress levels will be determined by measuring treatment-related changes in HRV. Using a wireless combination of a heart-rate belt and a tablet PC (VNS Analyse Professional, Commit GmbH, Liebenburg, Germany), a sitting electrocardiogram will be recorded after a short resting period. After automatic R wave identification, various HRV metrics will be determined. Of special interest are markers of parasympathetic regulation, such as the high-frequency component of HRV (0.15–0.4 Hz) and the root-mean square differences of successive R-R intervals, as well as markers of baroreflex regulation, such as the low-frequency component of HRV (0.04–0.15 Hz). Furthermore, by measuring HRV during acupuncture, distinct types of response to the stimulus can be explored and their potential influence on the efficacy of the treatment evaluated.

### Clinical examination for temporomandibular dysfunction

TMD will be diagnosed using the Research Diagnostic Criteria for Temporomandibular Disorders [27], which have been applied in many international studies. To ensure that the assessments are performed according to these criteria by a specialist, a research collaboration was established with the Department of Prosthetic Dentistry at the Hannover Medical School and a dentist was included in the study team (AW).

### Pain radiation

The precise headache pattern will be documented on a pain drawing created by the patient using an electronic pen on a tablet PC [28] running software SymptomMapper, which provides head outlines from four different views. Patients first choose descriptive terms for their pain and then color in all affected areas where they experience pain. Pain area and mean pain intensity will be calculated from these drawings.

### Pain gesture

Using a video recording of a patient’s pain body language (their pain gestures), their pain will be assessed before (T0) and 6 weeks after the intervention (T3). In addition to the location, which can be determined precisely by the pain gesture, the way the gesture is made will be discussed as a potential clinical sign in combination with the location. First, by analyzing the observed pain gestures, categories and pain clusters that may help in the diagnosis of tension-type headaches will be created according to the fascial distortion model described by Typaldos [29], because of the lack of previous studies. A fundamental aspect of how the cause of pain is identified in the fascial distortion model is through observing body language, which helps to give a precise differentiation of the symptoms. Then, these categories and pain clusters will be assessed for correlations with the TCM diagnoses.

### Data collection and management

All medical information will be documented and stored separately from personally identifiable data. The data will be recorded on the paper version of case report forms and double entered into a database by outcome assessors. The data sheets will be coded, and the group allocation will not be visible to third parties. Only pseudonymized data will be used for analysis and only members of the study group will be allowed to access these data to preserve patient confidentiality. The acupuncturist, physiotherapists, and statisticians will not have access to these data during patient evaluations. Independent data monitoring is performed by a scientist (JB) who is not involved in the study process. If subjects withdraw from the study, no further data will be collected from them. Data already obtained will be used in the intention-to-treat analysis with the consent of the patient or otherwise completely deleted from the database.

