### Patient recruitment

Patients will be invited to participate in the research study by notices in local and regional media and by calls for participation to staff members and students at the Hannover Medical School. Semi-structured telephone interviews and subsequent physical examinations will be performed to select patients with frequent episodic or chronic tension-type headaches according to the diagnostic criteria of the International Classification of Headache Disorders, 3rd Edition (IHS 2.2 and IHS 2.3).

After the telephone screening by two scientific assistants, a potential participant is registered and given an initial appointment, which includes a preliminary medical examination, checking of the inclusion and exclusion criteria, collecting comprehensive information, and providing consent to participate. After this appointment and consent to participate in the study, the subject draws one of the previously created opaque randomization envelopes, is assigned to the corresponding group, and is given dates for appointments for the intervention and for follow-up appointments. The appointments and schedules of the patients enrolled in the study are generated by a study nurse who is neither involved in the treatment nor in the randomization. Randomization will be overseen by one of the trial directors.

The total study period for each participant will be 7 months (Figs. 1 and 2). This period includes a 4-week baseline period, a 6-week intervention period, and a 20-week follow-up period. During the intervention period, the subjects in the trial groups will receive a total of 12 treatment units in decreasing frequency (three units per week during the first 2 weeks, two units per week during the third and fourth weeks, and one unit per week during the last 2 weeks). During the entire study period, as-needed analgesics (e.g. ibuprofen, aspirin, and paracetamol) can be taken as usual and will be documented in a headache diary.

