### Safety evaluation

All side effects that occur within the study period will be recorded. These will immediately be reviewed by the study physicians and will be considered in the evaluations. The study physicians will assess the relationship between the intervention and the severity of each adverse reaction. Independent safety monitoring will be provided by a researcher (CE) who is not involved in the study process and works with the university’s independent Medical Process and Patient Safety Unit. Suspected unexpected serious adverse reactions will be reported to the safety unit and the ethics committee. All study participants are covered throughout the trial by insurance. Due to the proven effectiveness of acupuncture and MTT, we consider that a loss of confidence by participants is unlikely. Patients may terminate their participation at any time for any reason. Participants may request a meeting with a study doctor to discuss an alternative treatment. To avoid dropouts, the participants will complete, at several time points, a survey on the organization, processes, possible problems, and their satisfaction with their interactions with the study staff.

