## Discussion

We expect to find positive treatment effects in all intervention groups for all outcomes in comparison with the usual care or control group. Furthermore, we expect to demonstrate the additive effects of acupuncture and MTT as a combination treatment and to provide scientific evidence to support the implementation of this complex health intervention. Since the two interventions differ in their mechanisms of action, consequently they exert analgesic, autonomic, and psychological effects at different levels. Thus, we expect different effects for each group for pain, the primary endpoint, and for the various secondary endpoints, such as mood, psychological stress, quality of life, and frequency of pain episodes. In addition, we believe that analyzing the correlations between the various outcome parameters with the applied treatment will provide information about the levels at which the effects occur. Furthermore, the influence of temporomandibular disorder on treatment effects will be a basic component of the data analysis. Figure 3 shows how the outcomes are related to each other. An evaluation of adverse events and their severity are important for safety and for patient acceptance of the treatment. Finally, these treatment modalities will be rated by the participating patients with regard to content and time requirements.

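### For participants who withdraw, the rule that data collection stops and stored data may be deleted conflicts with the rule that all side effects are recorded and evaluated

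*Protocol article*

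**What the plan says.** Two sections of the protocol article govern what happens to harm data.

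- Safety evaluation: "All side effects that occur within the study period will be recorded", followed by "These will immediately be reviewed by the study physicians and will be considered in the evaluations". The most serious class has its own route: "Suspected unexpected serious adverse reactions will be reported to the safety unit and the ethics committee". The same section gives an unrestricted right to leave: "Patients may terminate their participation at any time for any reason".
- Data collection and management: "If subjects withdraw from the study, no further data will be collected from them". For what is already on file: "Data already obtained will be used in the intention-to-treat analysis with the consent of the patient or otherwise completely deleted from the database".

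Patient recruitment fixes the period concerned: "The total study period for each participant will be 7 months". The Discussion states why harm data matter here: "An evaluation of adverse events and their severity are important for safety and for patient acceptance of the treatment".

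Neither section says which rule prevails when a participant withdraws, and the withdrawal rule does not treat safety data separately from other data.

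**The concern.** For a participant who withdraws, the two rules cannot both be followed in every case. Under the withdrawal rule, a side effect that appears or continues after withdrawal goes unrecorded, and one already on file can be removed.

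The reason for leaving may be the side effect itself. The missing harm data would then not be a random subset, and the comparison of harms by arm could look more favourable than it should. Feasibility and patient acceptance are stated aims of this trial, and the Discussion ties acceptance to the adverse-event evaluation. Arms are small, so a few lost records can change what an arm reports.

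**Working it through.** **Step 1. Apply both rules to each case.**

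| Case | Safety evaluation requires | Data collection and management requires | Compatible? |
|---|---|---|---|
| Side effect before withdrawal, consent given | record, review, evaluate | keep and use | yes |
| Side effect before withdrawal, consent not given | record, review, evaluate | delete from the database | no: it is recorded and reviewed, but cannot then be evaluated |
| Side effect after withdrawal, within the 7 months | record | collect nothing | no, if the study period runs for 7 months regardless of withdrawal |
| Suspected unexpected serious reaction before withdrawal, consent not given | also report to the safety unit and ethics committee | delete from the database | the report survives outside the database; its place in the arm comparison is not secured |

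**Step 2. Time left unobserved.** Patient recruitment gives 4 weeks of baseline, 6 of intervention and 20 of follow-up: 4 + 6 + 20 = 30 weeks, about 7 months. Withdrawal at the start of the intervention leaves 30 − 4 = 26 weeks uncollected. Withdrawal at its end leaves 30 − 10 = 20 weeks. A withdrawal during treatment therefore loses 20/30 = 67% to 26/30 = 87% of the planned period.

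**Step 3. How many participants the rule could reach.** Sample size estimation allows for 20% dropout, with 24 per arm and 96 in all.

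- Total: 0.20 × 96 = 19.2
- Per arm: 0.20 × 24 = 4.8

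This is a ceiling at the planned dropout rate. The 20% covers dropout of any kind, and the withdrawal rule applies only to formal withdrawals.

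**Step 4. Effect on an arm's harm figure (assumed numbers).** The article gives no adverse-event rate, no share of withdrawals due to harm and no refusal rate, so no expected loss can be derived. Suppose that *d* of 24 patients in an arm withdraw because of an adverse reaction, all refuse further use of their data, and nobody else in the arm has one. The true proportion is *d*/24:

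- *d* = 0: 0%, no loss
- *d* = 1: 1/24 = 4.2%
- *d* = 2: 2/24 = 8.3% (exact 95% CI 1.0% to 27.0%)
- *d* = 4: 4/24 = 16.7%

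After deletion the arm shows no events in each case. For *d* = 2 it would report 0/22, with exact upper 95% limit 1 − 0.025^(1/22) = 15.4%. If all randomised stay in the denominator it would report 0/24, with upper limit 1 − 0.025^(1/24) = 14.2%. The range shows sensitivity only; no value of *d* comes from the article.

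**The case against.** **Much harm data survives withdrawal.** With consent, everything obtained before withdrawal is kept and used. Side effects before withdrawal, normally including the one that prompts it, are recorded and reviewed at once, and suspected unexpected serious reactions are reported outside the trial database. Participants may also ask to see a study doctor. This stands. A reader might infer that reactions of patients who leave because of harm are never followed up or counted, and the article does not support that. The safeguards leave two gaps: the reporting route does not cover expected or non-serious reactions, and a meeting with a doctor concerns care, not recording.

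**The study period may end at withdrawal.** On that reading, stopping collection breaks no promise. The article does not exclude it, although it sets 7 months per participant without qualification. Even then the deletion conflict remains, and the outcome of an ongoing event is still unknown.

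**The loss need not be one-sided.** A reader might infer that only the three active arms can lose harm data, so that results must favour treatment. The Control group section lets usual-care patients continue analgesics and prophylaxis, and the safety rule covers all arms. They too can have side effects and leave because of them. Only the active arms can lose reactions to acupuncture or training, so a difference between arms is plausible, but it is not established. Nor does anything show that harmed patients refuse data use more often than others.

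**An article is condensed.** The full protocol or consent form may contain a safety exception. That would excuse silence. Here the article states two explicit rules that collide, and deletion is described as complete.

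**Conclusion.** The conflict is real but limited. It has two parts: side effects after withdrawal are not collected, and recorded ones can be deleted where consent is not given. The first part assumes that the study period continues to 7 months after a participant leaves; the second needs no such assumption.

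Because harm can cause withdrawal, the loss may be informative and may understate harm by arm. Neither the direction of any difference between arms nor the size of the loss can be established from the article. What can be said is that each patient lost from the harm count is 4.2 percentage points of an arm of 24, and that at the planned dropout rate at most about 19 of 96 participants, about 5 per arm, could come under the rule. The two sections should be reconciled before harms are analysed.

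**What to change.** Amend Data collection and management so that it agrees with Safety evaluation:

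1. Separate stopping treatment from withdrawing from the study. Participants who only stop treatment stay in outcome follow-up. The Dropout criteria section, which now excludes those who decline their allocated intervention, must be brought into line.
2. At withdrawal, ask the participant for agreement to keep adverse-event records in pseudonymised form and, separately, to record the outcome of any event still ongoing.
3. In all cases, report by arm, with all randomised as denominator, the anonymous number withdrawing because of an adverse event and the number whose data were deleted.

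Suggested wording: *Participants who stop treatment remain in follow-up. A participant who withdraws from the study is asked to agree that adverse events already recorded are retained in pseudonymised form and that the outcome of any ongoing event is recorded. The numbers withdrawing because of an adverse event, and the numbers whose data were deleted, are reported by arm out of all randomised.*

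The cost is an ethics amendment, since Study design requires the committee's written consent to any change, and one request to participants already enrolled. Trial status says recruitment closed in June 2019 and the study ends in January 2020, so consent wording at entry can no longer help. Where a participant refuses, only the anonymous count remains. Data already deleted cannot be recovered.

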### Statistical analysis

Descriptive statistics will be used to describe the study population. The comparability of the study groups regarding age, gender, and outcome characteristics will be determined using an analysis of variation (ANOVA) or chi-squared tests. A significance level of *p* < 0.05 will be used for all tests. Analyses will be performed on an intention-to-treat basis. Multiple imputation will be used to handle missing data. To test the primary hypothesis, potential interaction effects (time × intervention) with pain as the primary endpoint will be calculated using a repeated-measures ANOVA. Supplementary Bonferroni-corrected post hoc tests will assess potential intragroup effects. Secondary interval-scale outcome measures will be analyzed using the same strategy. The proportion of treatment responders (those with at least a 50% reduction in the frequency of pain episodes) will be determined in supplementary analyses for the various treatment arms.

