### Sample size estimation

The sample size calculation was based on the results of Endres et al. [17]. The study was powered to detect a small interaction effect of time × intervention dose (*f* = 0.15) for the primary endpoint (α = 0.05) with a power of 80% in a variance analysis with five repeat measurements and four study groups. With these targets, 20 patients per study group were required for analysis. Assuming a dropout rate of 20% over the course of the trial, 24 patients must be included in each study group; thus, recruitment of 96 participants is required. The sample size calculation was performed using the G*Power 3 software.

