### Outcome measurements

#### Primary outcome

To test the primary null hypothesis, the change in mean pain intensity (numerical rating scale) before the start of the intervention (T1) compared with the pain intensity 6 weeks after the end of the intervention (T3) is used as the primary endpoint.

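### The primary test, a time × intervention interaction sized for five measurements, targets neither the T1–T3 change that is the primary endpoint nor the between-group comparisons of the primary hypothesis

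*Protocol article*

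**What the plan says.** - **Endpoint** (Primary outcome): "the change in mean pain intensity (numerical rating scale) before the start of the intervention (T1"; the later occasion is T3, six weeks post-treatment. This is one contrast in time.
- **Hypothesis** (Research questions): acupuncture, training and their combination are each set against usual care, and the combination against each single treatment. That makes five between-group superiority comparisons.
- **Test** (Statistical analysis): "potential interaction effects (time × intervention) with pain as the primary endpoint will be calculated using a repeated-measures ANOVA". The section does not say which occasions enter. The follow-up tests it names are Bonferroni-corrected and within groups.
- **Sizing** (Sample size estimation): "The study was powered to detect a small interaction effect of time × intervention dose", with f = 0.15 and α = 0.05, "with a power of 80% in a variance analysis with five repeat measurements and four study groups". The result is 20 analysed per group, 80 in total. The section on secondary outcomes confirms that occasions run from T0 to T4.

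**The concern.** With four groups and five occasions, the interaction has (4−1)(5−1) = 12 degrees of freedom. It asks whether the arms' mean profiles differ in shape anywhere from T0 to T4. The endpoint asks only whether the arms differ in the T1–T3 change, which takes three degrees of freedom. A transient effect at T2, a late effect at T4 or a chance drift between T0 and T1 all feed the 12-degree-of-freedom test and say nothing about T3.

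The primary hypothesis could therefore be declared rejected when the declared endpoint shows no difference. Even a correct rejection would not say which arm beat which, and within-group follow-up tests cannot supply that.

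**Working it through.** **Inputs.** From the protocol: f = 0.15, α = 0.05, power 80%, k = 4 groups, m = 5 occasions, 20 per group (N = 80). The protocol gives neither the correlation ρ between occasions nor the sphericity factor ε. I assume ρ = 0.5 and ε = 1, and show ρ = 0.3 and 0.7 where it matters.

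**1. The plan's own figure.** For the interaction, λ = f²·N·m/(1−ρ), with (k−1)(m−1) and (N−k)(m−1) degrees of freedom.
- N = 80: λ = 0.0225 × 80 × 5 / 0.5 = 18.0, on 12 and 304 df; power 0.802.
- N = 76: λ = 17.1; power 0.775.

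So 20 per group is the smallest size that reaches 80%, and the stated figure is reproduced for five occasions.

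**2. If only T1 and T3 enter.** With m = 2, λ = 0.0225 × 80 × 2 / 0.5 = 7.2, on 3 and 76 df; power 0.58. On the same f and ρ, 80% power would need N = 128. At ρ = 0.7 the two-occasion power would be 0.82 (λ = 12.0), but the five-occasion power would then be 0.97. The stated size with five occasions fits ρ = 0.5, not 0.7.

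**3. Does the test isolate T1–T3?** Take outcome SD 1 and group effects in the ratio 0:1:1:2 (usual care, each single treatment, combination), scaled so that the interaction has f = 0.15. Put the whole effect at T2: combination minus usual care is then 1.06 SD at T2 and zero elsewhere. Because f is unchanged, λ is still 18.0 and the test still rejects with probability 0.80. A T1–T3 analysis rejects at 0.05. The same holds with the whole effect at T4. Over ρ = 0.3 / 0.5 / 0.7 the rejection rate is 0.62 / 0.80 / 0.97. In simulation (4,000 runs, Greenhouse–Geisser correction) the T2-only rate was 0.79 under equal correlations and 0.76 under first-order autoregressive correlation 0.7.

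**4. Analyses that do target T1–T3.** With 20 per arm, let S be the sum over arms of squared deviations of the T3 effects from their mean.
- Change score: λ = 20·S/[2(1−ρ)], on 3 and 76 df.
- ANCOVA of T3 on T1: λ = 20·S/(1−ρ²), on 3 and 75 df.
- Residual variance ratio, ANCOVA to change score: (1+ρ)/2 = 0.75 at ρ = 0.5.

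For an effect sustained over T2–T4, the T3 effects are 0, 0.433, 0.433 and 0.866, so S = 2 × 0.433² = 0.375. Then λ = 7.5 (change score) and 10.0 (ANCOVA).

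| Pattern, ρ = 0.5 | Five-occasion interaction | Change score | ANCOVA |
|---|---|---|---|
| Sustained T2–T4 | 0.80 | 0.60 | 0.74 |
| Growing (0.5, 0.75, 1) | 0.80 | 0.52 | 0.655 |
| Waning (1, 0.5, 0.25) | 0.80 | 0.28 | 0.36 |
| T3 only | 0.80 | 0.79 | 0.90 |
| T2 only or T4 only | 0.80 | 0.05 | 0.05 |

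**5. The five comparisons.** Sustained pattern, ANCOVA, 20 per arm, two-sided, residual SD √0.75 = 0.866:
- Combination against usual care (0.87 SD): noncentrality 0.866/(0.866·√(2/20)) = 3.16; power 0.88, or 0.70 at α = 0.05/5.
- The other four comparisons (0.43 SD): noncentrality 1.58; power 0.35, or 0.15 at α = 0.05/5.

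**The case against.** **The occasions are not stated.** If the ANOVA uses T1 and T3 only, its interaction F is exactly the between-group test of the change, and the endpoint is tested. That is correct, and a reader who infers that the endpoint is certainly untested goes too far. But the sample size section then describes a different test from the one that would be run. One of the two sections has to change on either reading.

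**ANCOVA is not simply more powerful.** A reader might infer that ANCOVA at T3 beats the planned test. The figures do not support that. ANCOVA beats a change score for the same endpoint, but the five-occasion interaction has higher power for sustained, growing and waning effects at ρ = 0.5. ANCOVA is ahead when the effect peaks at T3, or when correlation decays (sustained effect, autoregressive 0.7 with correction: 0.72 against 0.65). The power that the interaction draws from T2 and T4 is not power for the declared endpoint, but the difference is real and should be stated.

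**The scenarios are constructed.** The protocol gives no time course, SD or correlation. Effects confined to T2 or T4 show that the test can reject without any T1–T3 difference. They do not make 80% a forecast.

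**Sphericity.** A reader might also infer that an uncorrected F test is planned. The article does not say so, and a correction is commonly left to the analysis plan.

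**It is a pilot.** The abstract calls the study that and lists feasibility among its aims. The article nevertheless states a powered efficacy hypothesis, so the test should match it.

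**Conclusion.** The point holds as a mismatch between things the protocol states, not as missing detail. The named primary test, as sized, can be significant with no T1–T3 difference between arms: about 80% of the time for a T2-only or T4-only effect at the planned f (0.62 to 0.97 for ρ from 0.3 to 0.7, with ε = 1). The five superiority comparisons in the primary hypothesis have no between-group test of their own. The mismatch itself does not depend on the assumed correlation; the percentages do. The case for a T1-adjusted T3 analysis is that it answers the stated question, and does so more efficiently than a change score. It does not rest on greater power than the five-occasion test.

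**What to change.** Before outcome data are examined:

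1. Make the primary analysis the between-group contrasts at T3, adjusted for T1 mean pain intensity, by ANCOVA or by the T3 contrast of a mixed model. Name all five: each active arm against usual care, and the combination against each single treatment. A single test across arms would leave the primary hypothesis unresolved.
2. State a multiplicity rule for the five.
3. Make T2 and T4 contrasts secondary.
4. Bring the sample size section into line by restating power for these contrasts.

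**Cost.** No new data are needed, but the 80% power does not carry over. With 20 analysed per arm, a sustained effect and ρ = 0.5, the three-degree-of-freedom ANCOVA has power of about 0.74; 80% would take 23 analysed per arm. Four of the five pairwise contrasts have about 0.35, and less after a multiplicity adjustment. Recruitment ended in June 2019 according to the trial status, so this should be reported as a limit on what the trial can show, not met by enrolling more.
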